#### *Assignment to treatment group*

Participants are randomly assigned at the bedside to either Standard Care or Extended Care by research staff, in a 1:1 fashion in permuted blocks of eight randomization numbers. Randomization is stratified by two expected predictors of smoking cessation success, daily cigarette consumption in the month prior to admission (< 10 versus > = 10 cigarettes per day) and admitting service (cardiac versus other). Randomization is concealed by placing information about randomization condition into sealed envelopes. When a participant is randomized, the research staff member opens the next envelope corresponding to the participant’s randomization stratum, shares it with the participant, and initiates the assigned intervention. Research staff do not track the beginning and end of randomization blocks. Thus, neither the participant nor the research staff know participants’ randomization group before participants are enrolled.

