##### **Hospital admission characteristics**

Length of hospital stay, primary and secondary hospital discharge diagnoses, hospital service, and patient’s disposition after discharge (home or rehabilitation facility) will be obtained from hospital records.

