### Data analysis

#### *Sample size and power calculations*

We estimate that the primary outcome, verified seven-day tobacco abstinence rate at six-month follow-up, will be 20% among the Standard Care group and 35% among the Extended Care group. With a sample size of 165 per group, the study has 83% power to detect this difference with a 0.05 two-sided significance level. The estimate of the Standard Care cessation rate was extrapolated from three-month outcome data that was routinely collected from the MGH TTS. The rate ratio (35/20 = 1.75) was based on results of a recent meta-analysis
[8] but increased to reflect expected improvement due to project innovations.

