#### *Comparison of smoking status outcomes*

The primary analysis will be done using the intention-to-treat perspective, regardless of whether patients in the Extended Care group took medications or participated in the IVR intervention. In the primary analysis, patients who are not reached for follow-up or who have not validated smoking cessation (either a saliva cotinine < 10 ng/ml, CO < 9 ppm or proxy verification) will be considered to be smoking. A secondary analysis will use multiple imputation techniques for missing biochemical verification values. Cross-sectional analyses will be conducted for outcomes assessed at one, three and six months after discharge.

Chi-square tests will be used to compare smoking cessation rates between the Extended Care group and the Standard Care group at each time point. Logistic regression analysis will be used to compare the two groups with age, sex, discharge diagnosis (cardiac versus other) and cigarettes smoked per day as the additional factors in the model. A longitudinal analysis using Generalized Estimating Equations (GEE) techniques will be used to assess the overall impact including data from all follow-up times while accounting for similarity in patient data across multiple assessment points. In a secondary analysis, we will use multiple imputation techniques for missing biochemical or proxy validation data. Self-reported seven-day point prevalence abstinence is the principal secondary endpoint.

Other smoking status outcomes compared between groups will be: (1) continuous abstinence; (2) prolonged abstinence (defined as quit at one, three and six months); (3) time to slip or relapse (first cigarette smoked after discharge); and (4) making a quit attempt (defined as intentionally not smoking for ≥ 24 hours) after discharge. Continuous and sustained abstinence and whether or not the participant made a quit attempt will be assessed using chi-square tests and logistic regression. Time to relapse will be assessed using survival analysis with Cox proportional hazards models. A secondary hypothesis is that participants in the Extended Care group will have higher rates of using smoking cessation pharmacotherapy and counseling than the Standard Care group. Use of pharmacotherapy and counseling will be assessed using chi-square tests.

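### Neither the chi-square nor the adjusted model uses the strata as randomised: admitting service is a stratifier, but discharge diagnosis takes its place in the model, at a small cost in power

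*Protocol article*

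**What the plan says.** All references are to the Protocol article.

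- **Assignment to treatment group:** "Randomization is stratified by two expected predictors of smoking cessation success, daily cigarette consumption in the month prior to admission" (cut at 10 per day) and "admitting service (cardiac versus other". Allocation is "in a 1:1 fashion in permuted blocks of eight randomization numbers". On timing: "Participants are randomly assigned at the bedside to either Standard Care or Extended Care by research staff".
- **Comparison of smoking status outcomes:** "Chi-square tests will be used to compare smoking cessation rates between the Extended Care group and the Standard Care group at each time point". No stratification is mentioned. Then: "Logistic regression analysis will be used to compare the two groups with age, sex, discharge diagnosis (cardiac versus other) and cigarettes smoked per day". Admitting service is not in the covariate list, and the section does not say whether the chi-square or the logistic model is the primary test.
- **Hospital admission characteristics:** the items taken from hospital records include "primary and secondary hospital discharge diagnoses, hospital service", listed as separate variables.
- **Sample size and power calculations:** the verified six-month rate "will be 20% among the Standard Care group and 35% among the Extended Care group", with 165 per group, 83% power and a two-sided 0.05 level.

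**The concern.** Blocking within strata forces the arms to be nearly balanced on the two factors. If those factors predict quitting, which is the protocol's own reason for choosing them, the balance removes part of the chance variation in the difference between arms. A plain chi-square does not know this. Its variance still includes the between-stratum part, so it rejects less often than its nominal level and gives up some power.

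The adjusted model could have repaired this, but it matches only one stratifier. The cardiac-versus-other split is carried over from the randomisation, yet it is attached to a different variable. A patient admitted to a non-cardiac service can leave with a cardiac diagnosis, and the reverse. Admitting service had to be known to choose the envelope, whereas the discharge diagnosis is settled later. At stake are some efficiency and the agreement between design and analysis.

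**Working it through.** **1. The plan's own power figure.** Inputs: 20% and 35%, 165 per arm, two-sided 0.05.

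- Without continuity correction: SE under the null = sqrt(2 x 0.275 x 0.725 / 165) = 0.04916. SE under the alternative = sqrt((0.20 x 0.80 + 0.35 x 0.65) / 165) = 0.04846. Power = Phi((0.15 - 1.96 x 0.04916) / 0.04846) = Phi(1.107) = 86.6%.
- With continuity correction: 165 per arm supports 83.6% (83% needs 163 per arm).

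The stated 83% therefore reproduces as an unstratified two-proportion test with continuity correction.

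**2. How conservative the chi-square is.** The article gives no stratum sizes or quit rates, so these are assumptions: stratum weights w = 0.08, 0.22, 0.20, 0.50 and three sets of Standard Care rates p. With arms balanced within strata and no treatment effect, the true variance of the difference is proportional to sum of w x p(1 - p). The chi-square uses pbar(1 - pbar). With R the ratio of the first to the second, the actual type I error is about 2[1 - Phi(1.96 / sqrt(R))].

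| Assumed stratum rates | pbar | sum of w x p(1 - p) | pbar(1 - pbar) | R | Type I error |
|---|---|---|---|---|---|
| 0.35, 0.28, 0.20, 0.13 | 0.195 | 0.1511 | 0.1567 | 0.964 | 4.6% |
| 0.45, 0.35, 0.18, 0.12 | 0.209 | 0.1522 | 0.1653 | 0.920 | 4.1% |
| 0.50, 0.40, 0.15, 0.08 | 0.198 | 0.1351 | 0.1588 | 0.851 | 3.4% |

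**3. Power at the planned 15-point difference.** Same weights and rates, N = 330, blocks of eight, with the within-stratum odds ratio set so that the overall difference is 15 points (6,000 simulated trials each):

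| Range of stratum rates | Chi-square | Stratified CMH | Gain |
|---|---|---|---|
| 13-35% | 87.8% | 88.4% | 0.6 points |
| 12-45% | 86.8% | 88.7% | 1.9 points |
| 8-50% | 88.7% | 92.0% | 3.3 points |

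**4. A second set of assumptions.** 30% on a cardiac service, 70% smoking >=10 per day, overall rates of 20% and 35%, and stratum odds ratios of equal strength in opposite directions (4,000 trials each; simulation error about 0.0035 for type I error and 0.005 for power):

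| Odds ratio per factor | Type I error, chi-square / CMH | Power, chi-square / CMH |
|---|---|---|
| 1 | 0.054 / 0.052 | 0.869 / 0.868 |
| 1.5 | 0.048 / 0.050 | 0.865 / 0.866 |
| 2 | 0.044 / 0.049 | 0.868 / 0.875 |
| 3 | 0.040 / 0.048 | 0.883 / 0.900 |

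Logistic regression on the true strata performs like CMH. Replacing service with a diagnosis that disagrees with it in 10% of patients (assumed) changes power by at most about 0.5 point.

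**5. A trap in the arithmetic.** The odds ratio for 20% versus 35% is (0.35/0.65) / (0.20/0.80) = 2.15. That is a marginal odds ratio. If it is applied inside the 8-50% strata, the Extended Care rates become 0.683, 0.589, 0.275 and 0.158. Their weighted mean is 0.08 x 0.683 + 0.22 x 0.589 + 0.20 x 0.275 + 0.50 x 0.158 = 31.8%, against 19.8% in Standard Care. Power then falls to 72% (chi-square) and 78% (CMH), mainly because the assumed effect has shrunk from 15 to 12 points.

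**The case against.** The strongest reply is that this is an efficiency preference. The chi-square is a valid comparison of the randomised arms and errs on the safe side. The adjusted model already has cigarettes per day and a cardiac term. The article is condensed, so the full protocol or SAP may stratify the primary test, and discharge diagnosis may be loose wording for the stratifier.

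Much of this stands. It limits the size of the point, and three stronger readings that a reader might infer are not supported:

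- **Inflated false positives.** Ignoring prognostic strata lowers the type I error. In no scenario is it raised beyond simulation error.
- **An underpowered trial.** At the planned difference the unstratified chi-square stays above the stated 83% in every scenario. The 72% versus 78% contrast rests on the smaller effect shown in the last step of the working and should not be cited as the cost of ignoring strata.
- **A biased adjusted analysis.** The discharge diagnosis is settled after randomisation, but before discharge the arms differ only in the delivery of take-home medication, and the automated calls start two days after discharge. No plausible route from allocation to a cardiac diagnosis is apparent.

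The loose-wording defence is weaker, because the article itself lists discharge diagnoses and hospital service as separate items. Nor does silence about which test is primary help, since neither one uses the strata as randomised.

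**Conclusion.** The point holds as a mismatch between design and analysis with a small, one-sided cost. The article stratifies on two factors, tests without them, and adjusts for one of them plus a different variable in place of the other. The consequence is a mildly conservative chi-square: a type I error of roughly 3.4% to 5% against a nominal 5%, and about 0.5 to 2 points of power forgone with moderate strata. The loss reaches about 3 points only if quit rates run from 8% to 50%, a best-to-worst odds ratio of (0.50/0.50) / (0.08/0.92) = 11.5. If the strata are not prognostic, there is no loss.

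The direction follows from the design. The sizes rest on assumed stratum weights and quit rates, and the effect of swapping the covariate rests on an assumed 10% disagreement. The documents give none of these. The change is worth making because it costs almost nothing, not because the planned result would be unsafe.

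**What to change.** - Name the primary test of the six-month validated outcome and make it a CMH test, or a logistic model, on the two factors as randomised: <10 versus >=10 cigarettes per day, and admitting service cardiac versus other.
- Report the stratum-adjusted risk difference with its confidence interval.
- In the adjusted model, replace discharge diagnosis with admitting service, and state the form in which cigarettes per day enters.
- Keep the crude chi-square as supportive. A model with discharge diagnosis can stay as a sensitivity analysis.

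The cost is analysis wording only. Both factors were recorded to select the envelope, so no data collection and no change in sample size are needed. The change should be dated before the outcome data are analysed by arm. The Trial status section places the end of follow-up in November 2012.

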#### *Utilization of acute health care services*

We hypothesize that the Extended Care group will have a lower rate of acute health care utilization than the Standard Care group in the six months after hospital discharge. Logistic regression will be used to determine whether the Standard Care group was more likely to have any hospital admissions or emergency room visits and Poisson regression models will be used to determine whether the Standard Care group had a higher number of admissions or hospital days
[45].

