##### Post-discharge utilization of acute health care services

We assess emergency room visits and hospital readmissions during the six months after the discharge from the hospitalization at which enrollment occurred. Emergency room visits and hospitalizations are assessed two ways. First, an electronic medical record tracking system automatically notifies study staff whenever any participant is admitted to any emergency room or hospital in the Partners HealthCare System, the integrated health care delivery system to which MGH belongs. Second, participants are asked at each follow-up survey whether they have been to an emergency room or been hospitalized since their index hospital discharge. Questions are adapted from the 2008 National Health Interview Survey (‘Were you seen in an emergency room but not admitted to the hospital during the six months after you left MGH on (discharge date)?’; ‘Were you hospitalized anywhere overnight during the six months after you left MGH on (discharge date)? Do not include an overnight stay in the emergency room.’). These allow us to identify a hospitalization or emergency room visit made by a participant to a hospital outside Partners system. We request discharge summaries for admissions to hospitals outside Partners HealthCare System. Measures for health care utilization after discharge consist of: (1) number of hospital readmissions; (2) number of hospital days; (3) number of emergency room visits; (4) total number of hospitalizations and emergency room visits.

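### Poisson regression is named for hospital days, which cluster within stays; with model-based standard errors the 5% test of days would be falsely significant in about one third to two thirds of null trials

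*Protocol article*

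**What the plan says.** The Measures part of the protocol article, under Post-discharge utilization of acute health care services, fixes the window: "We assess emergency room visits and hospital readmissions during the six months after the discharge from the hospitalization at which enrollment occurred". It then lists the counts: "Measures for health care utilization after discharge consist of: (1) number of hospital readmissions; (2) number of hospital days", followed by emergency room visits and a combined total of hospitalizations and emergency visits.

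Under Data analysis, Utilization of acute health care services, the article gives a directional hypothesis: "We hypothesize that the Extended Care group will have a lower rate of acute health care utilization than the Standard Care group". Two kinds of model follow. For the binary outcome, "Logistic regression will be used to determine whether the Standard Care group was more likely to have any hospital admissions or emergency room visits". For the counts, "Poisson regression models will be used to determine whether the Standard Care group had a higher number of admissions or hospital days". A literature reference is attached to that sentence. Nothing is said about a dispersion parameter, a robust variance or a negative binomial alternative.

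The Background section places reduced acute-care use within an exploratory aim. The primary outcome is validated abstinence at six months.

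**The concern.** A Poisson model with its ordinary standard errors takes the variance of each patient's count to equal its mean. That may be roughly right for the number of admissions. It cannot be right for days in hospital unless every stay lasts one day. Days within a stay are not separate events: one readmission of a week adds seven to the count at once, while a patient who is not readmitted contributes zero. The model treats those seven days as seven independent pieces of information, so the standard error is too small and the p-value too low.

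At stake is a stated hypothesis of the trial. A chance imbalance in a few long stays could be reported as a significant reduction in hospital days, or as a significant increase.

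**Working it through.** **Inputs from the article.** Planned size is 165 per group, with a two-sided 0.05 level stated for the primary outcome and assumed here for utilisation as well. Allocation is 1:1 and the window is six months. The article gives no admission rate, length of stay or variance, so these are assumed and varied.

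**The plan's own figure.** The only power statement concerns abstinence: "With a sample size of 165 per group, the study has 83% power to detect this difference with a 0.05 two-sided significance level", where the rates "will be 20% among the Standard Care group and 35% among the Extended Care group". With 165 per group this gives 86.6% without a continuity correction and about 83.6% with one. The stated 83% is therefore reproduced with the correction, and 165 per arm is used below. There is no corresponding figure for utilisation.

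**Step 1: variance-to-mean ratio.** Let m be the mean number of admissions per patient and L the length of a stay.

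- If admissions are Poisson, the ratio for days is φ = E[L²]/E[L] = mean stay × (1 + CV²). It does not depend on m.
- If admission rates also vary between patients (gamma-Poisson with shape k), φ for admissions is 1 + m/k, and φ for days rises by (m/k) × mean stay.

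**Step 2: true error of the nominal 5% test.** With model-based standard errors it is 2 × [1 − Φ(1.96/√φ)].

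| Situation | φ | Error |
|---|---|---|
| Every stay exactly 1 day | 1 | 5.0% |
| Every stay exactly 3 days | 3 | 26% |
| Every stay exactly 4 days | 4 | 33% |
| Mean 3 days, CV 0.7: 3 × 1.49 | 4.47 | 35% |
| Mean 5 days, CV 1: 5 × 2 | 10 | 54% |
| Mean 6 days, CV 1.2: 6 × 2.44 | 14.64 | 61% |
| As above, with m = 0.8, k = 0.5: 14.64 + 1.6 × 6 | 24.24 | 69% |

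An error of exactly 50% needs φ of about 8.44. The rows with identical stays show that the problem does not depend on a long tail of stays.

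For admissions, the most dispersed case (m = 0.8, k = 0.5) gives φ = 1 + 1.6 = 2.6 and an error of 22%. If admissions are Poisson, the error is 5%.

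**Step 3: check by simulation.** There were 4,000 null trials per scenario with 165 per arm. Mean admissions were 0.3, 0.5 or 0.8, either Poisson or gamma-Poisson with shape 2, 1 or 0.5. Stays were gamma-distributed and rounded to whole days, with mean/CV of 3/0.7, 5/1.0 or 6/1.2.

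| Outcome | φ | Model-based error | Robust or Pearson-scaled error |
|---|---|---|---|
| Hospital days | 4.4 to 23.5 | 35% to 68% | about 4.5% to 7% |
| Admissions | 1.0 to 2.6 | 5% to 22% | about 4% to 6% |

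With a mean stay of 5 days and CV 1, the model-based error for days is 53% to 64%. All these rates count both directions. A false result favouring Extended Care occurs about half as often, roughly 17% to 34% for days.

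**The case against.** The strongest reply is that one sentence in a condensed article names a model family and does not say how the variance is estimated. Poisson regression with a robust or scaled variance is still Poisson regression and is valid here. An analysis plan that is not shown may specify it, and so may the attached reference, which is not available. This stands in part: the size quoted above is conditional on model-based standard errors, and the article does not state that these will be used. It does not remove the point. The article chose the model, applied it alike to two very different counts, and for days the default inference from that model is wrong by a wide margin under every assumption tried.

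Three stronger readings are tempting, and the article does not support them.

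- A reader might infer that the whole utilisation hypothesis would be falsely confirmed about half the time. The large inflation concerns hospital days only. For admissions it ranges from none to moderate, and the logistic analysis of any admission or emergency visit is untouched. A figure of one half is a mid-range value under assumed inputs and cannot be derived from the article.
- A reader might tie the error to the Discussion's argument about insurance coverage. That argument concerns readmissions and emergency room use, not days. The cost-effectiveness measure is cost per quit, and the cost table lists no hospital-day costs.
- A reader might add that a time-at-risk offset, adjustment for the randomisation strata or a permutation test is missing. The article sets a common six-month window, no size has been shown for these omissions, and such details are commonly left to the analysis plan.

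**Conclusion.** The point holds for hospital days, and to a lesser and uncertain degree for number of admissions. If model-based standard errors are used, the nominal 5% test of days would be falsely significant in roughly one third to two thirds of null trials, both directions combined. This assumes 165 per arm, 0.3 to 0.8 admissions per patient, a mean stay of 3 to 6 days and a coefficient of variation of 0.7 to 1.2. For admissions the error is about 5% to 22%. That days are overdispersed follows from the structure of the outcome and needs no outside data; only the exact size depends on the assumptions. The analysis is secondary or exploratory, and the primary abstinence comparison is not affected. The change is worth making, but nothing in the trial's main conclusion depends on it.

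**What to change.** In Data analysis, Utilization of acute health care services, state that number of admissions and number of hospital days will be analysed in the log-link model with a robust (sandwich) or Pearson-scaled variance. Negative binomial regression is a reasonable alternative for admissions. The logistic analysis can stay as it is.

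This is a software option and needs no new data. The cost is wider confidence intervals: on the log scale they grow by about √φ, which for days is √4.4 ≈ 2.1 to √23.5 ≈ 4.8 times under the assumptions above. That width reflects the information actually present.

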#### *Cost effectiveness*

Cost-effectiveness analyses will be assessed by cost per quit as the main outcome to ensure maximum comparability with other published studies
[46,47]. The incremental costs per quit are estimated as follows: (Total costs of Extended Care - Total costs for Standard Care)/(Total successful quits at six months for Extended Care - Total successful quits at six months for Standard Care). The major costs tracked in the study are described in Table
2. In the intervention arm, these include Tobacco Counselor time (based on hourly wage), the cost of the IVR service, the cost of providing a free pharmacotherapy to participants after discharge, and the cost of any additional counseling or pharmacotherapy used by participants. The major costs in the Standard Care arm that require tracking are the use of post-discharge counseling or pharmacotherapy. For both study arms we will track the portion of counseling and therapy costs (exclusive of the 90-day supply of pharmacotherapy specific to the intervention) paid for by participants out of pocket versus by insurance. Prospective collection of cost information (for example counselor time) will maximize the accuracy of our data.

**Table 2 T2:** Cost data collection domains

**Resource**	**Description**	**Source of resource use data**	**Source of cost data**
Tobacco counselor time – pre-discharge	Initial assessment (Counselor chart review and meeting with the patient to determine a quit plan), medication recommendations, and counseling	Study records	Human resources data
Tobacco counselor time – post-discharge	Medication and cessation support, time spent trying to reach subjects	Study records, survey responses	Human resources data, published reports and datasets
IVR service	Automated telephone outreach to smokers.	Study records	Study records
Smoking cessation medications	FDA-approved smoking cessation medications provided to patients at discharge from the hospital and subsequent refills (includes mailing costs)	Study records	Hospital billing data
	Smoking cessation medications obtained by patients after discharge	Survey responses	Red Book 2010 [48]

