### Participants

#### Inclusion criteria

MGH inpatients are eligible for the study if they:

· Are an adult (≥18 years old).

· Are a current daily smoker (smoked ≥ 1 cigarette/day in the past month when smoking in their usual pattern).

· Plan to sustain or initiate a quit attempt after hospital discharge, assessed by asking the smoker to endorse one of four options (‘I will stay quit’, ‘I will try to quit’, ‘I don’t know if I’m going to quit’, ‘I do not plan to quit’). Only those smokers who endorse the first two responses are eligible for study enrollment.

· Have received smoking cessation counseling (for more than five minutes) and post-discharge smoking cessation medication recommendations from the MGH Tobacco Treatment Service staff.

· Are being discharged to home or, if discharged to a rehabilitation facility, have a mobile telephone on which they can receive the IVR calls.

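### Incremental cost per quit is defined from unscaled arm totals, and the article does not say that pre-discharge counselling, which both arms receive, is counted in both arms or in neither

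*Protocol article*

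**What the plan says.** The Cost effectiveness section of the protocol article makes cost per quit the main outcome of that analysis and gives its formula in words, which begins "Total costs of Extended Care - Total costs for Standard Care)/(Total successful quits at six months for Extended Care"; the denominator then subtracts the corresponding count in the comparison arm. Neither the numerator nor the denominator is divided by the number of participants in the arm.

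On what is costed, the text says of Extended Care: "In the intervention arm, these include Tobacco Counselor time (based on hourly wage), the cost of the IVR service", followed by the free drug and any further counselling or drug. Of Standard Care it says: "The major costs in the Standard Care arm that require tracking are the use of post-discharge counseling or pharmacotherapy". Table 2 has two rows for counsellor time. The pre-discharge row, which has no arm label, is described as "Initial assessment (Counselor chart review and meeting with the patient to determine a quit plan), medication recommendations, and counseling".

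The inclusion criteria require that every participant "Have received smoking cessation counseling (for more than five minutes) and post-discharge smoking cessation medication recommendations from the MGH Tobacco Treatment Service staff". According to Study recruitment and Assignment to treatment group, this happens before consent and randomisation. Under Interventions, Standard Care receives the inpatient protocol, and Extended Care receives standard care plus the two added components.

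**The concern.** There are two separate issues.

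First, a ratio of differences in totals mixes the programme's effect with the difference in arm size. An extra participant in one arm adds that arm's mean cost to the numerator and that arm's quit rate to the denominator, and neither is an effect of treatment. The smaller the true difference in quit rates, the larger the distortion.

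Second, a cost incurred by everyone before randomisation must cancel in an incremental analysis. It cancels if it is counted in both arms or in neither. The section makes it a tracked domain, names counsellor time under one arm, and describes the other arm's tracking as post-discharge only. It does not say how the shared visit is handled, so an analyst following the text could charge it to Extended Care alone.

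Cost per quit was chosen for comparability with published studies, and the Background hopes that cost-effectiveness information may encourage insurers to expand coverage. The figure should therefore be free of avoidable artefacts.

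**Working it through.** **Inputs from the article.** 165 per arm, 330 in all; abstinence 20% (Standard Care) and 35% (Extended Care); 1:1 allocation in permuted blocks of eight; 2 x 2 = 4 strata; median counselling visit 20 minutes.

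**Assumed inputs, because the article gives no unit costs.** Mean cost per participant $300 (Extended Care) and $60 (Standard Care); counsellor wage $25-60 per hour; a smaller effect of 26% versus 20% for illustration.

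**The article's own figure.** There is no cost figure to reproduce. The stated 83% power uses the same arm sizes and quit rates. With a continuity correction, power = Φ[(0.15 - 1/165 - 1.96 × √(2 × 0.275 × 0.725/165)) / √((0.20 × 0.80 + 0.35 × 0.65)/165)] = 83.7%, so these inputs are consistent with it.

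**Arm totals against per-participant ratio.**

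Totals: (nE·cE - nS·cS) / (nE·pE - nS·pS). Per participant: (cE - cS) / (pE - pS).

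Per-participant values: 240/0.15 = $1,600 at 35% versus 20%; 240/0.06 = $4,000 at 26% versus 20%.

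| Extended/Standard | 35% v 20% | Shift | 26% v 20% | Shift |
|---|---|---|---|---|
| 165/165 | 39,600/24.75 = $1,600 | 0% | 39,600/9.90 = $4,000 | 0% |
| 167/163 | 40,320/25.85 = $1,560 | -2.5% | 40,320/10.82 = $3,726 | -6.8% |
| 163/167 | 38,880/23.65 = $1,644 | +2.7% | 38,880/8.98 = $4,330 | +8.2% |

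**How unequal the arms can be.** Imbalance arises only in the last, incomplete block of each stratum. A block stopped at r of 8 can be out by at most min(r, 8 - r), which is 4 at r = 4. Since 330 = 8 × 41 + 2, the four remainders must sum to 2 modulo 8. Four remainders of 4 sum to 16 and are excluded. The worst admissible set is 4, 4, 4 and 6 (sum 18), giving 4 + 4 + 4 + 2 = 14, that is 172/158. If all admissible sets of remainders are taken as equally likely (an assumption), about 96% of allocations differ by 4 or less, so 167/163 is a fair outer case.

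**Shared counselling charged to one arm.** 20 minutes at $25-60 per hour is 25/3 = $8.33 to 60/3 = $20 per participant. Divided by 0.15 this adds $56 to $133 per quit. Charged to both arms or to neither, with per-participant scaling, it adds $0.

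**The case against.** **Arm totals.** For a 1:1 design planned at 165/165 the formula is ordinary shorthand. At equal arms it is exactly right, and at the likely splits it is wrong by about 3% or less at the planned effect. This stands as to size. It does not make the stated rule correct, and scaling costs nothing. A reader might multiply four strata by a maximum of four and infer a possible difference of 16. The planned total of 330 rules that out, and even the ceiling of 14 is very improbable.

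**Counselling.** A reader might infer that the article does charge the bedside visit to Extended Care alone. It does not say so. Table 2 carries no arm label, counsellor time under Extended Care can mean the post-discharge return calls, and the Standard Care sentence speaks only of major costs that need tracking. A shared cost may need no tracking precisely because it cancels. That holds only if the visit is also left out of Extended Care, and the section does not say that it is.

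**Drug prices.** A reader might also infer that the same product is priced differently by arm, because study-supplied drug is valued from hospital billing data and other drug from Red Book 2010. The documents do not support that as an error. Table 2 splits by supply channel: the row "Smoking cessation medications obtained by patients after discharge" has no arm label, and the text counts additional drug use in Extended Care too. Pricing each channel from its own source is a defensible costing choice. With no unit prices given, neither the size nor the direction of any distortion can be shown.

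**Status.** The Background calls cost-effectiveness an exploratory aim, which limits the weight of the whole point.

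**Conclusion.** The point holds in two limited parts. The formula as written is correct only for equal arms. At a split of 167/163 the error is -2.5% to +2.7% at 35% versus 20%, and about -7% to +8% at an assumed 26% versus 20%, in both cases with assumed costs of $300 and $60. The treatment of pre-discharge counselling is ambiguous. On the unfavourable reading it adds $56-133 per quit at an assumed $25-60 per hour, which is about 3-8% of the illustrative $1,600 (56/1,600 and 133/1,600). No dollar amount here comes from the article. The abstinence endpoints are not touched.

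**What to change.** Define the ratio as (mean cost per randomised participant, Extended Care minus Standard Care) / (quit proportion among those randomised, Extended Care minus Standard Care). Add one sentence stating that pre-discharge counsellor time is counted in both arms or in neither. Re-pricing all cessation drugs from a single source is at most an optional sensitivity analysis.

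The cost is two changes of wording. No new data are needed, because arm sizes, costs and quits are already collected, and the change can be made at analysis.
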